**Figure 2. F2:**
[figure not shown]
Compendium of study design.

Measurements will be got by 2 operators, intensive care physicians, trained in using bedside USG in the ICU. The standardization of USG measurements was previously published, whose correlation analysis found an excellent interobserver relationship (*R*2 > 0.90)^[28]^

Care will be taken during the handling of patients so that all measurements do not entail greater risks for them, except for the discomfort caused by the exam. The same examiner will make all measurements and, at the same point, as we will mark the studied limb with a marker pen and cover with plastic film.

We will perform the tomographic control exams of the thigh only in the studied region through the marking performed, to reduce: radiation dose to patients, costs and exam time. The CT analyzes will be interpreted by a radiologist and we will have 3 images per patient.

### 3.4. Statistical analysis

Initially, the Shapiro–Wilk test will be performed to evaluate the data distribution. Mean or median depending on the distribution of variables will describe data. To compare the values of quadriceps femoris thickness, Student’s t test or Wilcoxon test for paired samples will be applied, depending on the distribution of variables. Bland & Altman test will also be performed to assess the agreement between the methods. The relationship between caloric and protein intake, laboratory alterations and loss of muscle mass will be evaluated through multiple linear regression, with muscle mass being considered a dependent variable and caloric and protein offers and laboratory alterations being independent variables. We will use the STATA version 14 program for the analyses.

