## Abstract

**Methods and analysis::**

The aim of the present study is to measure muscle mass loss by measuring the thickness of the rectus femoris muscle by bedside ultrasound in critically ill patients admitted to the Intensive Care Unit (ICU) of a university hospital. Information will be collected regarding the length of hospital and ICU stay, the reason for admission, anthropometric data at admission and during hospitalization, energy needs, nutritional therapy used, and fasting time. This is a prospective, observational study that will be carried out in a single center in an ICU of a tertiary university hospital. The study population will undergo 3 tomographic images and 3 ultrasounds of the rectus femoris of each patient at different times. We propose, unprecedentedly, performing a validation study of ultrasound with the gold standard Computed tomography to evaluate the musculature of critically ill patients victims of traumatic brain injury. The results got will texto be fundamental for the development of new fields of investigation and certainly contribute to the discovery of a new approach to treat sarcopenia in critically ill patients. The Research Ethics Committee approved the study and all patients included will sign an informed consent form. (Clinical Record: RBR-2bzspnz).

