### 1.2. Research hypothesis

The assessment of skeletal muscle mass through ultrasound agrees with the gold standard method CT.

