## 2. Study objectives

### 2.1. Primary outcome

The primary endpoint will be muscle group (quadriceps) thickness. The agreement of quadriceps thickness will be verified between the images got through point-of-care ultrasound, a fast, low-cost, noninvasive method available in the ICU versus CT, the gold standard for assessing muscle thickness.

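### Agreement between ultrasound and CT is the primary question, but section 3.4 names a paired difference test first and does not say which analysis, or what result, decides it

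*Protocol article*

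**What the plan says.** Section 1.2 of the protocol article states one hypothesis: "The assessment of skeletal muscle mass through ultrasound agrees with the gold standard method CT". Section 2.1 makes thickness of the quadriceps the primary endpoint and says "The agreement of quadriceps thickness will be verified between the images got through point-of-care ultrasound" and CT. Section 2.3 describes the design as a validation of ultrasound.

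Section 3.4 gives the analysis in two steps. The first is "To compare the values of quadriceps femoris thickness, Student’s t test or Wilcoxon test for paired samples will be applied", with the choice between the two tests left to the distribution of the variables. The second is "Bland & Altman test will also be performed to assess the agreement between the methods".

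The abstract foresees "3 tomographic images and 3 ultrasounds of the rectus femoris of each patient at different times", so each patient can contribute up to three ultrasound-CT pairs. The article does not say which of the two analyses is primary. It gives no acceptable bias, no acceptable width for the limits of agreement, no sample size and no expected SD of the differences.

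**The concern.** A paired t or Wilcoxon test asks whether the mean or median difference is zero. Agreement also depends on how far apart the two methods are in individual patients, which is the spread of the differences. The paired test treats that spread as noise. For a given non-zero bias, a noisier ultrasound makes a non-significant result more likely. A small bias measured precisely can be significant although the methods are interchangeable in practice.

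Bland-Altman addresses the right quantity, but it returns estimates. Unless someone has said beforehand how wide the limits may be, it gives no verdict. As section 3.4 stands, the only one of its two analyses with a ready-made yes or no is the one that does not measure agreement. At stake is whether the conclusion on the primary hypothesis rests on a criterion fixed in advance.

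**Working it through.** **Plan's own figure.** There is none to reproduce: the article states no sample size, alpha, power, bias, SD or margin. Everything below uses assumed values, one pair per patient, and a two-sided 5% level.

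**Formulas.** Bias b and SD of differences s are in % of thickness.
- Limits of agreement: b ± 1.96 s.
- Chance that the paired t test is significant: from the non-central t distribution with n-1 degrees of freedom and non-centrality (b/s)√n.

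**Results.**

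| Assumed b, s | Limits of agreement | Significant, n=30 | Significant, n=60 |
|---|---|---|---|
| 0, 25 | 0 ± 49.0 = -49% to +49% | 5% | 5% |
| 5, 20 | 5 ± 39.2 = -34% to +44% | 26% | 48% |
| 5, 10 | 5 ± 19.6 = -15% to +25% | 75% | 97% |
| 1, 2 | 1 ± 3.92 = -2.9% to +4.9% | 75% | 97% |

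- Row 1: the test is non-significant in 95% of studies at any n, although a single ultrasound reading may be out by half the thickness.
- Rows 2 and 3: with bias held at 5%, doubling the SD from 10% to 20% raises the non-significant share from 25% to 74% at n=30, and from 3% to 52% at n=60. Noise makes the result look better.
- Rows 3 and 4: both have b/s = 0.5, so the test behaves identically, although the limits in row 3 are five times as wide. The test sees only the ratio of bias to spread.

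**The same pattern in millimetres, again assumed.**
- Bias 1 mm, SD 5 mm (limits -8.8 to 10.8 mm): significant in 14% of studies at n=20 and 28% at n=50.
- Bias 0.5 mm, SD 0.5 mm (limits -0.48 to 1.48 mm): significant in 80% at n=10 and 99% at n=20.

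**How far the Bland-Altman verdict depends on the limit.** The approximate half-width of the 95% CI for each limit of agreement is t × s × √(1/n + 1.96²/(2(n-1))), which is 0.814 s at n=20 and 0.645 s at n=30. Suppose agreement is declared when the CIs of both limits lie inside the acceptance limit. By simulation with n=20, zero bias and SD 1 mm, the chance of declaring agreement is about 2% for ±2 mm, 58% for ±3 mm and 99% for ±4 mm. The same study can therefore pass or fail according to a number the article does not give.

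**A possible benchmark from the article.** Section 1.1 cites muscle loss reaching 65% in 42 days. Scaled to one week, that is 65/42 × 7 = 10.8% if linear, or 1 - 0.35^(7/42) = 16.1% if exponential. This shows why limits of ±35% to ±49% would be of little use, but it is not a limit to adopt:
- It scales an upper figure, while section 4 places the greatest losses in the first days or week.
- Cross-method limits are a different quantity from change tracked by ultrasound alone, where a constant bias cancels.
- It may be unattainable. With zero bias, SD 5% and n=30, the outer bound is 1.96 × 5 + 0.645 × 5 = 9.8 + 3.2 = 13.0%, already beyond 11%.

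**Repeated pairs.** With three pairs per patient and within-patient correlation ρ of the differences, the variance of the mean bias is 1 + (3-1)ρ times the value obtained if pairs were independent. The factor runs from 1 at ρ=0 to 3 at ρ=1. Treating all pairs as independent would generally make the intervals too narrow.

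**The case against.** The strongest reply is that Bland-Altman is planned, and that section 3.4 uses the word agreement only for it. This stands. Bias and limits of agreement will be estimated, and readers can judge them. A reader might infer that the study intends to call ultrasound valid whenever p exceeds 0.05, or that its hypothesis cannot be shown or refuted at all. The document supports neither: it nowhere makes a p-value the criterion for validity. The percentages above describe what the paired test would do if used for that purpose, not a rule the investigators have adopted.

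Second, this is a condensed article, and a numerical limit could sit in a fuller protocol or SAP. That also stands, so a missing number alone would be a weak point. It does not remove the other half: the article itself puts a difference test first for an agreement hypothesis and leaves open which analysis decides.

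Third, the sentence on the paired test does not name what is compared, and with three measurement times it could mean change over time. The next sentence's opening, which adds Bland-Altman to what went before, and section 3.1, which has CT and ultrasound thickness compared to validate the method, make ultrasound versus CT the more natural reading. If time points are meant, the text should say so.

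Finally, keying the choice of test to the distribution of the variables, and calling Bland-Altman a test, are matters of wording. Neither shows that the wrong distribution will be checked.

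**Conclusion.** The point holds in this form. Section 3.4 does not say which of its two analyses decides the primary hypothesis or what result counts as agreement, and the one it lists first cannot establish agreement. On the assumed inputs, the paired test is non-significant in 95% of studies with limits of ±49% and significant in 75% to 97% with limits of -2.9% to +4.9%. Those sizes rest on assumed bias, SD and n, but the direction does not: the test responds only to bias relative to spread.

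Bland-Altman as planned will give valid material for a judgement. What is open is whether that judgement will be made against a limit set before or after the data are seen. This concerns the primary hypothesis and should be settled before analysis.

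**What to change.** Reword section 3.4 as follows:

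1. Name Bland-Altman as the primary analysis. Report mean bias and both 95% limits of agreement, each with a 95% CI computed by a method that allows for up to three pairs per patient.
2. Before analysis, state a maximum acceptable difference between ultrasound and CT, justified by the investigators, and judge the limits of agreement and their CIs against it. The one-week figure of about 11% is an illustration only. If a limit already exists in a fuller document, cite it here.
3. Report the paired comparison as mean bias with its CI, and state that it is not evidence of agreement. If the t or Wilcoxon test was meant for change over time, say so.
4. Check normality and constant spread on the paired differences, and use log or ratio limits if the spread grows with thickness.

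The cost is a rewritten paragraph and one justified number; no new data are needed. The downside is that the study can then fail its hypothesis, or be inconclusive if the intervals around the limits are wide.

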**Figure 1. F1:**
[figure not shown]
Illustrative photo to characterize the gained images (CT and USG). CT = computed tomography, USG = ultrasonography.

The measurement will be performed with the patient in a supine position with the leg extended and relaxed, at the midpoint between the anterosuperior iliac spine and the proximal edge of the patella, where the quadriceps femoris will be visualized, a muscle group in the thigh, formed by 4 muscles: vastus medialis, intermedius, lateral and rectus femoris.^[15]^ Subsequently, we will use planimetric techniques to measure distances and areas: Thickness: from the muscle-fat interface to the muscle-muscle interface or from the muscle-fat interface to the bone surface,^[8]^ forming a straight horizontal line and; manually describing the thickness of the quadriceps femoris.

Measurements will be got at the time of admission of the patient to the hospital, preferably still in the trauma room, within 24 hours of the trauma. Second measurement 24 hours to 96 hours after admission, preferably in the ICU and third measurement 96 hours to 168 hours after admission. All USG measurements will be performed simultaneously with quadriceps CT, with a maximum interval of 12 hours between 1 technique and another. The study protocol is represented in Figure 2.

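### Three ultrasound/CT pairs per patient feed the primary agreement question, but the methods named assume independent differences; if the visits are pooled, confidence intervals are too narrow and the paired test rejects too often

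*Protocol article*

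**What the plan says.** Section 2.1 sets one primary question: whether quadriceps thickness by bedside ultrasound agrees with CT.

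The data for it are repeated within patients. The Abstract plans "3 tomographic images and 3 ultrasounds of the rectus femoris of each patient at different times", and section 3.3 (text after Figure 2) confirms for CT that "we will have 3 images per patient". The first pair is taken at admission. For the others, section 3.3 (text after Figure 1) says: "Second measurement 24 hours to 96 hours after admission, preferably in the ICU and third measurement 96 hours to 168 hours after admission". At each time the two techniques are paired, "with a maximum interval of 12 hours between 1 technique and another". The text after Figure 2 adds that one examiner measures at a point marked on the limb and kept visible. Section 3.1 states that the follow-up pairs, too, are compared in order to validate the method.

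Section 3.4 compares thickness by a paired Student's t test or a Wilcoxon test, chosen by the distribution, and adds: "Bland & Altman test will also be performed to assess the agreement between the methods". It names the software, Stata 14. It does not mention patient, visit, clustering or a repeated-measures version of either method.

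**The concern.** The paired test and the ordinary Bland-Altman analysis each treat every ultrasound-minus-CT difference as independent. Here three differences come from the same limb of the same patient at the same marked site. A persistent patient-specific offset between the methods is plausible, and it would make those differences positively correlated. Counting 3n pairs as 3n independent observations then claims more information than the study has.

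At stake is the stated precision of the primary result: the standard error of the bias, any interval around the bias or the limits of agreement, and the paired p-value. A pooled analysis without a time term would also hide any change in bias over the first week.

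**Working it through.** The article gives no sample size, correlation or standard deviation, so there is no figure of its own to reproduce. The check asks what pooling would do.

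**Inputs**
- Pairs per patient: m = 3 (Abstract; section 3.3).
- Within-patient correlation ρ of the ultrasound-minus-CT differences: assumed, 0.1 to 0.8. It concerns the differences, not muscle thickness itself.
- Patients: n = 20, 30 and 60, assumed, for the simulation only.
- Simplifications: constant bias, equal correlation between visits, normal differences, all three pairs present.

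**Bias and paired t test, visits pooled**

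Design effect: DE = 1 + (m − 1)ρ = 1 + 2ρ. Naive width relative to correct width = 1/√DE. True coverage of a nominal 95% interval = 2Φ(1.96/√DE) − 1. True test size = 1 − coverage.

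| ρ | DE | Naive/correct width | Coverage | True size of 5% test |
|---|---|---|---|---|
| 0 | 1.0 | 1.00 | 95.0% | 5.0% |
| 0.1 | 1.2 | 0.91 | 92.6% | 7.4% |
| 0.3 | 1.6 | 0.79 | 87.9% | 12.1% |
| 0.5 | 2.0 | 0.71 | 83.4% | 16.6% |
| 0.8 | 2.6 | 0.62 | 77.6% | 22.4% |

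Example at ρ = 0.5: 1.96/√2.0 = 1.386, and 2Φ(1.386) − 1 = 0.834.

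Simulation (20,000 runs per setting) agrees: coverage for the bias was 87.5–87.8% at ρ = 0.3 and 82.8–83.4% at ρ = 0.5 over the three sample sizes.

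**Limits of agreement, visits pooled**

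With N = 3n pairs and true variance 1, the expected pooled variance is (N − DE)/(N − 1).
- n = 20, ρ = 0.7: (60 − 2.4)/59 = 0.976.
- n = 60, ρ = 0.3: (180 − 1.6)/179 = 0.997.

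The standard deviation is thus at most about 1% too small over ρ = 0.3 to 0.7 (√0.976 = 0.988), and the limits hardly change. Their intervals do suffer: simulated coverage of the interval around the upper limit was about 91% at ρ = 0.3, 87% at 0.5 and 81–82% at 0.7.

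**Each visit analysed separately**

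Simulated coverage for the bias was 94.8–95.1% in every setting. Nothing is too narrow, but there are three estimates of bias and three pairs of limits.

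**Variance components**

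Summing the between- and within-patient variance gave 1.00 on average against a true value of 1 in every setting.

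**The case against.** The strongest reply is that the article never says the visits are pooled. Section 3.1 describes the comparison visit by visit, and a paired test with a Bland-Altman plot at each visit fits sections 3.1 and 3.4 and is valid. This stands, and it makes the point conditional. A reader might infer that the error bars are bound to be too narrow; the documents do not support that, because it needs both pooling and a positive correlation. What remains is that section 2.1 poses one agreement question and section 3.4 gives no way to combine or choose among three visit-specific answers.

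A second reply is that a journal article may leave such detail to a fuller document. This lowers the severity. It does not remove the point, because section 3.4 does name the methods, the rule for choosing the test and the software, and the methods as named do not allow for the repeated pairs.

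Third, the correlation is unknown. True muscle thickness largely cancels in the difference, so shared anatomy alone does not make ρ high. Section 3.3 also speaks both of two operators and of a single examiner, so a shared examiner effect is uncertain. The low values therefore belong in the range: at ρ = 0.1 the loss of coverage is small, and at 0 there is none.

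Two further inferences are tempting and should be resisted.
- One is that the error favours declaring ultrasound valid. Narrow intervals do overstate certainty about agreement. But a paired test that rejects too often signals false differences, which works against the hypothesis in section 1.2. Section 3.4 also states no confidence interval and no margin for acceptable agreement, so there is no decision rule to tilt.
- The other is that the limits will be too narrow because each patient's three pairs are averaged. Averaging is proposed nowhere.

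**Conclusion.** The concern holds in conditional form. The primary methods named in section 3.4 assume independent differences, while the design supplies three per patient and uses them all for validation. If they are pooled as independent, a nominal 95% interval for the bias covers about 93% to 78% and a 5% paired t test has a true size of about 7% to 22% as ρ runs from 0.1 to 0.8. The limits of agreement are almost unaffected; the intervals around them are not. If the visits are analysed separately, the intervals are valid but the primary question has three answers.

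These sizes rest on an assumed ρ and on the simplifications listed above; the test sizes are for the t test, not the Wilcoxon test. The point should be fixed, but it is not a demonstrated error, since the text does not commit to pooling.

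**What to change.** In section 3.4, name a Bland-Altman analysis for repeated measures in which the true value changes:
- Fit a linear mixed model to the ultrasound-minus-CT differences, with a random patient effect and time point (three levels) as a fixed effect.
- Set the limits of agreement at the bias ± 1.96 × √(between-patient + within-patient variance). Do not use the standard deviation of patient means, which understates the spread (about 0.81 of its true value at ρ = 0.5).
- Take confidence intervals from the model or from a bootstrap that resamples patients.
- Report the bias by time point from the same model, and let this model replace a paired test on pooled pairs.

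If visit-specific analyses are preferred, say so and state which visit answers the primary question.

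The cost is a few lines of Stata and intervals that may be wider than those from naive pooling. No new data or measurements are needed.

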### 2.2. Secondary outcome

The secondary outcome will include nutrition of trauma patients, associating the loss of muscle mass with caloric and protein intake and laboratory changes caused by the stress of traumatic brain injury, such as levels of creatinine, albumin, total protein fractions, protein c reactive, blood count, platelet count and bilirubin.

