### 3.3. Study procedures

#### 3.3..1.
*Study protocol*.

Anthropometric, clinical and nutritional data will be collected: height, weight, BMI, injury severity score,^[21]^ prognostic scores SAPS-3^[22,23]^ and APACHE II,^[24]^ number of days of mechanical ventilation and ICU and hospital stay,^[3]^ NUTRIC score,^[25]^ NRS 2002^[26]^ and basal energy expenditure through pocket formula with calorie and protein requirements.

Weight will be measured on a Stryker scale stretcher, height will be used standard body tape measure, measurements will be taken at the time of admission of the patient to the ICU. BMI will be classified according to the World Health Organization 1995.^[27]^

Daily, the volume of diet and protein intake will be recorded until the seventh day of hospitalization, and the percentage of diet intake will then be calculated by the ratio of the amount actually ingested to the amount prescribed.

The USG will be performed with a Sono Site M-Turbo device with 2-dimensional mode, with a linear transducer (frequency: 7–13MHz) to get high-resolution images of surface structures 1, in cross-section, in B-mode, with the transducer oriented transversely to the longitudinal axis (the imaginary line marked before) of the thigh forming a 90° angle in relation to the skin surface with minimal pressure on the skin (Fig. 1).

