Another observational study,^[34]^ aimed to evaluate the role of muscle ultrasound in the analysis of nutritional status in 29 patients admitted to the ICU, identified the greatest loss of muscle mass in the first week of hospitalization, having a direct association with the patient’s nutritional status. Although BMI is a commonly used parameter for screening nutritional status, it does not show the amount of muscle loss in these patients.^[35,36]^ In contrast, USG is a valuable and practical measurement tool that may hold promise in helping to guide metabolic support that allows morphological changes in muscles to be assessed in critically ill patients.^[37]^

It is also important to note how safe and viable the tool is. In patients with severe trauma, the use of quadriceps USG was easy to perform and reliable even in the hands of less experienced operators.^[38]^ Thus, USG ends up gaining ground for its ease of use and lower costs.

Our study can contribute to the use of USG in critically ill patients with muscle loss, not only by recognizing patients with a more fragile nutritional component but also by differentiating the more severe patients who are at greater risk of unfavorable evolution in the ICU. We believe USG is a noninvasive and easy-to-operate tool to distinguish patients on mechanical ventilation who have muscle wasting by analyzing quadriceps thickness, and thus early approaches could be applied to optimize treatment.

The novelty and importance of this project lies in using a method for assessing muscle mass through ultrasound of the quadriceps femoris, a noninvasive, low-cost bedside method that is feasible in critically ill patients.

In this study, we propose, unprecedentedly, performing a validation study of ultrasound with the gold standard (GS) to evaluate the musculature of critically ill patients victims of traumatic brain injury. The results got will be fundamental for the development of new fields of investigation and may contribute to the discovery of a new approach to treat sarcopenia in critically ill patients.

This study has limitations, such as the characterization of the study population in terms of age and sex, trauma severity, fluid balance, and associated comorbidities, which can affect both muscle thickness and outcomes. In addition, this is an observational study in a single center, which certainly has limitations in the patient profile and regional variations.

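### The nutrition regression contradicts itself on its outcome (loss of muscle or muscle mass) and lists no admission thickness, body size or severity term, although all are collected

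*Protocol article*

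**What the plan says.** Section 2.2 gives the secondary aim as "associating the loss of muscle mass with caloric and protein intake and laboratory changes caused by the stress of traumatic brain injury". Section 3.4 begins in the same terms: "The relationship between caloric and protein intake, laboratory alterations and loss of muscle mass will be evaluated through multiple linear regression". The same sentence then specifies the model, "with muscle mass being considered a dependent variable and caloric and protein offers and laboratory alterations being independent variables". Nutrition is called intake in the first half of that sentence and offers in the second.

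Section 3.3 shows what will be available. Thickness is measured at hospital admission, within a day of the trauma, and then twice more: "Second measurement 24 hours to 96 hours after admission, preferably in the ICU and third measurement 96 hours to 168 hours after admission". Weight, height, BMI, the injury severity score, SAPS-3 and APACHE II are recorded. Requirements come from "basal energy expenditure through pocket formula with calorie and protein requirements", and the formula is not given. Section 3.3 also defines a percentage of diet intake, the amount taken divided by the amount prescribed.

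The Discussion lists as limitations "age and sex, trauma severity, fluid balance, and associated comorbidities, which can affect both muscle thickness and outcomes".

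The article gives no sample size, effect size or error rate for this regression.

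**The concern.** Thickness at follow-up and loss since admission are different outcomes, and regressing each on feeding answers a different question. A level with no baseline term mainly ranks patients by the muscle they arrived with. If larger patients are also prescribed more, thickness and feeding will be associated whether or not feeding affects wasting.

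Severity is a separate problem and arises with either outcome. If sicker patients take less of their feed and also waste faster, feeding and loss are associated through severity. The plan collects three severity scores and names trauma severity as a factor, but the listed predictors contain none of them.

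At stake is the interpretation of the only analysis described for the secondary outcome. An association between feeding and muscle could be read as bearing on wasting when it reflects body size or severity.

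**Working it through.** The plan states no figure for this regression, so there is none to reproduce. The check compares the text with itself and then sizes the consequence under stated assumptions.

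**1. Outcome.** Section 2.2 and the first half of the regression sentence in section 3.4 say loss. The second half says muscle mass. Admission thickness is measured, so a change or a baseline-adjusted analysis is possible, but neither is named.

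**2. Predictors.** Listed: caloric and protein offers, laboratory alterations. Collected but not listed: admission thickness, weight and BMI, and three severity scores. Age and sex are named in the Discussion as affecting thickness and are not listed either.

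**3. How much of a level is baseline.** Let the SD of loss be k times the SD of admission thickness, with the two uncorrelated (assumption). The share of follow-up variance due to admission thickness is 1/(1 + k²):

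- k = 0.2: 1/1.04 = 96%
- k = 0.3: 1/1.09 = 92%
- k = 0.5: 1/1.25 = 80%

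**4. Association through body size alone.** Suppose thickness correlates 0.5 and calories 0.7 with weight (assumptions), with no other link. The induced correlation is 0.5 × 0.7 = 0.35. Over inputs of 0.3–0.6 and 0.5–0.9 it runs from 0.3 × 0.5 = 0.15 to 0.6 × 0.9 = 0.54. At an assumed n = 60, t = 0.35 × √(58/(1 − 0.35²)) = 2.85, p = 0.006. That is a single-predictor test, and the plan enters calories and protein together. If protein also correlates 0.7 with weight, and calories and protein correlate 0.5 / 0.7 / 0.9, the calorie coefficient has p = 0.10 / 0.24 / 0.52. The joint test of both stays at p = 0.006 to 0.02.

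**5. Simulation with a true nutrition effect of zero.** 1000 runs per setting, nominal level 5%. All inputs are assumptions: n = 30, 60, 100; correlation of admission thickness with weight 0.3 or 0.5; k = 0.3; severity loading 0, 0.3 or 0.5 on intake fraction, a laboratory marker and loss. The table gives the range of false-positive rates for nutrition.

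| Model | Nutrition entered as | Severity 0 | Severity 0.3 | Severity 0.5 |
|---|---|---|---|---|
| Level, no baseline, no severity | absolute, weight-scaled | 13–77% | 15–82% | 20–92% |
| Level, no baseline, no severity | % of prescription | 4–5% | 5–6% | 6–8% |
| Loss or baseline-adjusted, no severity | either | 4–6% | 6.5–13% | 11–51% |
| Baseline-adjusted plus severity | either | 4–6% | 4–7% | 4–6% |

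The Monte Carlo standard error at 5% is √(0.05 × 0.95/1000) = 0.7 percentage points, so the last row is close to nominal. The second row is low because baseline variation hides the severity effect. Once that variation is removed (third row), confounding by severity shows. Correcting the outcome alone is therefore not enough.

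**6. Precision.** If admission and follow-up thickness correlate r = 0.8 / 0.9 / 0.95 (assumptions), baseline adjustment leaves residual variance 1 − r² = 0.36 / 0.19 / 0.0975. Against an unadjusted level, that is worth 2.8 / 5.3 / 10.3 times the patients. Against a simple change score with equal variances, the ratio is 2(1 − r)/(1 − r²) = 2/(1 + r) = 1.11 / 1.05 / 1.03.

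**The case against.** The strongest defence is that muscle mass in the second half of the sentence is shorthand for loss, since the first half and section 2.2 both say loss. That reading is possible. A reader might infer that the plan has chosen a level over loss; the text does not support so firm a statement. What stands is the contradiction, and the absence of a severity term matters under either reading.

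A reader might also infer that the result will mostly reflect size and severity. The document does not show this. The size bias needs a level outcome and nutrition entered as an absolute weight-related amount. The formula is not given, and section 3.3 defines a percentage of prescription, under which the harm is mainly lost precision. The share due to severity is unknown, and C-reactive protein, creatinine, platelets and bilirubin may capture part of it. Nothing in the plan suggests that they capture all of it.

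Two figures invite overstatement. The p-value of 0.006 does not apply to the calorie coefficient in the planned model. The 2.8- to 10-fold gain disappears almost entirely if loss was intended all along.

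It is also tempting to say that three correlated readings are put into an ordinary regression. Section 3.3 provides three CT images per patient, but section 3.4 does not say that they are pooled. One loss value per patient would raise no such problem.

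Finally, covariates are often left to an analysis plan, and the Discussion admits the limitation. But section 3.4 did not leave the model open: it named the outcome and the predictors. Admitting a confounder as a limitation does not adjust for it when a measure of it is being collected. The plan already speaks of association and relationship, so it makes no causal claim that needs withdrawing.

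**Conclusion.** The point holds as a contradiction about the outcome together with a predictor list that is too narrow. Taken literally, the model can largely reflect admission muscle size: 80–96% of follow-up variance for k between 0.5 and 0.2. The resulting size bias is serious only if nutrition is an absolute weight-related amount. With either outcome the model is open to confounding by severity, although with a level outcome and percentage of prescription this was largely hidden by noise in the simulated settings. All sizes rest on assumed correlations, loadings and sample sizes, because the article supplies none.

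This should be fixed, but it does not threaten the study's main result. The hypothesis and primary endpoint concern agreement between ultrasound and CT and are untouched.

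**What to change.** Reword the regression sentence in section 3.4 as follows.

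- **Outcome:** follow-up thickness adjusted for admission thickness. Change from admission with admission thickness as a covariate gives the same nutrition coefficient and is equally acceptable.
- **Covariates:** age, sex, weight or BMI, and one severity score chosen in advance from those already collected.
- **Nutrition variable:** per kg of body weight, or the percentage of prescription already defined in section 3.3. Use one term throughout in place of both intake and offers.
- **Repeated readings:** if both follow-up readings are used, a linear mixed model with a random patient effect.
- **Laboratory values:** keep the list in this model short, or examine those variables separately.

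No new measurements are needed. The cost is a few degrees of freedom. Because the article does not give the sample size, that cost cannot be weighed exactly, which is the reason for limiting the laboratory list.
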